# EHLS at School: school-age follow-up of the Early Home Learning Study cluster randomized controlled trial

**DOI:** 10.1186/s12887-018-1122-y

**Published:** 2018-05-02

**Keywords:** School-age assessment, Long-term follow-up, Home learning environment, Cohort study, Education, Early childhood, Parenting

## Abstract

**Background:**

Targeted interventions during early childhood can assist families in providing strong foundations that promote children’s health and wellbeing across the life course. There is growing recognition that longer follow-up times are necessary to assess intervention outcomes, as effects may change as children develop. The Early Home Learning Study, or ‘EHLS’, comprised two cluster randomized controlled superiority trials of a brief parenting intervention, *smalltalk*, aimed at supporting parents to strengthen the early childhood home learning environment of infants (6–12 months) or toddlers (12–36 months). Results showed sustained improvements in parent-child interactions and the home environment at the 32 week follow-up for the toddler but not the infant trial. The current study will therefore follow up the EHLS toddler cohort to primary school age, with the aim of addressing a gap in literature concerning long-term effects of early childhood interventions focused on improving school readiness and later developmental outcomes.

**Methods:**

‘EHLS at School’ is a school-aged follow-up study of the toddler cluster randomized controlled trial (*n* = 1226). Data will be collected by parent-, child- and teacher-report questionnaires, recorded observations of parent-child interactions, and direct child assessment when children are aged 7.5 years old. Data linkage will provide additional data on child health and academic functioning at ages 5, 8 and 10 years. Child outcomes will be compared for families allocated to standard/usual care (control) versus those allocated to the *smalltalk* program (group program only or group program with additional home coaching).

**Discussion:**

Findings from The Early Home Learning Study provided evidence of the benefits of the *smalltalk* intervention delivered via facilitated playgroups for parents of toddlers. The EHLS at School Study aims to examine the long-term outcomes of this initiative to determine whether improvements in the quality of the parent-child relationship persist over time and translate into benefits for children’s social, academic and behavioral skills that last into the school years.

**Trial registration:**

8 September 2011; ACTRN12611000965909 (for the original EHLS)

## Background

In Australia, 23% of children entering primary school have failed to acquire the developmental skills essential for success in the school environment [1]. Children from socially and economically disadvantaged families are particularly vulnerable to poorer development of early socio-emotional, language and cognitive skills [2–8]. Early childhood is a key period in which targeted interventions can support families in providing their children with strong foundations for health and wellbeing across the life course [9, 10].

Achievement of good developmental outcomes by disadvantaged children is associated with a rich home learning environment in early childhood [1, 11]. These environments are characterized by frequent positive parent-child interactions, such as verbal exchanges, where parents respond to and build on the child’s interests, and use books, toys and other materials to extend the child’s developing skills [12]. The quality of the home environment exerts strong and lasting effects on children’s development, independently of other community or educational factors or interventions [13–17]. The United Kingdom Effective Pre-School, Primary and Secondary Education Project (1997–2013, N ≈ 3000) found that the quality of the home learning environment at age 3 predicted children’s reading and numeracy at ages 5 and 7 years (effect sizes from .50 to .73), and their literacy, English, mathematics and science attainment at age 10 (effect sizes from .29 to.49). The effects of the home learning environment were stronger than socio-economic status, parent education or income (at 3, 5 and 7), and the quality of pre-school and primary school experiences at age 10 [11].

Effective intervention to promote an enriched home learning environment for vulnerable children is hampered by a lack of evidence. Interventions to enhance the learning environment of childcare settings have shown benefits [18, 19]. Only a few studies internationally have sought to enhance the quality of the learning environment at home, and while promising, these are limited by small sample sizes and short-term follow-ups [20, 21]. In Australia, we are aware of two programs in use that seek to enhance the home learning environment [22, 23]. Neither has been the subject of a rigorous evaluation using a randomized controlled trial design and the long-term effects on the home learning environment and children’s outcomes are unknown.

The Early Home Learning Study (EHLS, 2009–2013) [24] was a community-based effectiveness trial of *smalltalk*, a new program designed to help parents in disadvantaged circumstances provide an enriched home environment to enhance the development of their young children (aged 6–36 months). The *smalltalk* program was developed in partnership with the State Government of Victoria, Australia, and was evaluated by the EHLS [25]. The EHLS comprised two cluster randomized controlled trials conducted in parallel, each delivered by a non-specialist workforce within one of two existing services: a 6-week maternal and child health parenting group program for parents of infants aged 6–12 months, and a 10-week facilitated playgroup program for parents of toddlers aged 12–36 months.

Twenty two local government authorities participated across the two trials, with up to six community locations (clusters) nominated for program delivery within each. Clusters were randomly allocated to one of three trial conditions: intervention (*smalltalk group-only*); enhanced intervention with home coaching (*smalltalk plus*); and ‘standard care’/usual practice (control). Participants received the intervention that was offered by the location servicing their geographic region. Between 2010 and 2012, programs were delivered to 2228 families attending 389 groups in 101 sites with 94 staff trained to provide either standard or *smalltalk* programs (not both). Reach, retention, satisfaction and program fidelity were good to excellent [26]. Eighty-four percent of referred families agreed to participate. Across the three conditions, participants attended an average of 59–64% of group sessions. Further details of the intervention format and delivery are listed elsewhere [24].

Parent-child interactions, the home environment and children’s communication and social skills were assessed at baseline (0 weeks), post-intervention (12 weeks) and follow-up (32 weeks) [25]. In the infant trial, there were no differences by trial arm on the primary outcomes at 32 weeks. In contrast, in the toddler trial, consistent benefits of the *smalltalk* program were evident at 32 weeks, including parent-reported improvements in the home learning environment (effect sizes 0.16 to 0.17), and most substantively, improvements in the directly observed parent-child interactions (effect sizes 0.46 to 0.55) [25]. Other findings included positive effects on child development for toddlers, with a 37% reduced odds of poor child social skills for *smalltalk* vs. control; and consistently greater gains for families receiving home coaching (i.e., ‘*smalltalk plus’*) compared to the *smalltalk group-only* program (unpublished findings, available on request) [26]. Given these results, the current study aims to follow participants from the toddler trial (and not the infant trial) to school age. In the absence of longer-term outcome data for the toddler cohort, it is unknown whether early gains will translate into improved developmental skills for children at school age, with ongoing health, social and economic benefits.

The skills that children bring with them as they enter primary school lay critical foundations for subsequent behavioral, social and academic skills [10]. The previous research findings from the EHLS indicated that families can be supported to enrich the home environment for toddlers from disadvantaged backgrounds with a fairly ‘light touch’, brief community-based intervention, yet we do not know if these effects are sustained sufficiently to improve school readiness and later developmental outcomes at school. Follow-up of the EHLS toddler cohort in early primary school will address a major gap in current evidence, and will provide foundations for better targeting of early interventions to support children at risk of poor developmental outcomes. There is growing recognition that long follow-up times are necessary as intervention effects may change as children develop [17], and the deleterious effects of social disadvantage tend to become stronger over time [18, 27]. Internationally, there is limited prospective evidence regarding the long-term effectiveness of early interventions, and particularly limited knowledge of the effects of intervention on vulnerable children under five [28]. Our proposed school-age assessment will address this gap and provide robust evidence of the extent to which an early childhood home learning intervention helps to reduce socio-economic inequalities in early child development.

The Differential Susceptibility Hypothesis [29–31] suggests that some children and parents are more sensitive to specific environmental experiences, and thus to intervention, than others. These effects are not identified using the traditional evaluation approach of averaging intervention effects, given that some parents and children may respond well or very well, while others are less affected. A school-age assessment of the large EHLS cohort also provides an opportunity to evaluate children’s sensitivity to changes in parenting and the home learning environment and to map the differential effects of the *smalltalk* intervention on child outcomes, in the context of (a) individual factors (e.g. child self-regulation), and (b) other parent and family contextual factors (e.g. parent mental health, adverse life events).

## Methods/design

### Aims

This follow-up study, EHLS at School, is focused on the toddler cohort who participated in the facilitated playgroup intervention arm. The decision to limit the school-age follow-up to the toddler cohort was required by resource availability that limited follow-up to one intervention arm of the EHLS. Findings from the EHLS indicated that substantive gains from the *smalltalk* intervention were observed in the toddler trial (parents of toddlers 12–36 months), compared to the infant cohort where gains were not maintained. The study aims are to:investigate the effects of the toddler parenting program *smalltalk* on children’s school readiness, social and emotional development, and academic functioning;investigate whether initial gains in parent-child interactions and the home environment are maintained to age 7.5;identify the program attributes (program intensity, quality and timing) associated with gains in parent-child interactions, the home environment and child outcomes;examine whether the benefits of *smalltalk* are affected by individual child and family factors such as self-regulation, and parent and family contextual factors; anddetermine the financial, health and education costs and cost-effectiveness of *smalltalk*.

### Study design

The EHLS at School Study is a prospective cohort study involving the school-age follow-up of the EHLS toddler cohort (aged 12–36 months at baseline), with direct data collection from participants occurring when children are 7.5 years old. Additional outcome data will be available via data linkage when children are aged 5, 8 and 10 years. Data collection for the study commenced in early 2016 and is expected to continue until December 2018. Participants in the *smalltalk* and *smalltalk plus* groups will be analyzed together, and are subsequently referred to as simply ‘*smalltalk*’. Note that all research staff are blinded to participants’ original allocation to the *smalltalk* or standard group conditions for all aspects of data collection.

### Eligibility criteria

For the current study, participants in the toddler trial (*n* = 1226) who completed an assessment prior to, and post intervention, or at the 32 week follow-up (the majority of participants completed both assessments; 93%) were re-contacted for participation. Participants who declined to be contacted for future research or those who actively withdrew from the EHLS were excluded. Participants were identified as eligible for the original EHLS study if the family had a child in the target age range and met at least one risk factor for socio-economic disadvantage (i.e., parent < 25 yrs., low parent education, single parent, low family income, Aboriginal or non-English speaking background). Families with insufficient oral English to complete assessments or families who would benefit from more intensive support services were excluded. Sample characteristics from the EHLS are documented elsewhere [25]. Participant flow in the EHLS and estimated follow-up participation in EHLS at School are shown in Fig. 1.

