### Power calculation

Given the high rate of retention in the EHLS (78% to 32 week follow-up), we anticipate 65% participation in EHLS at School of eligible participants (i.e., *n* = 212 standard; *n* = 455 *smalltalk* participants). For the comparison of the *smalltalk* to standard programs, the study provides over 95% power to detect a minimum effect size of 0.3, or 88% power to detect an effect size of 0.25, at *p* < 0.05.

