### Recruitment strategy

In EHLS at School, children are eligible to be assessed when they reach 7.5 years of age. Given that toddlers in the original EHLS were aged 12–36 months at baseline assessment over 2010–2013, children are eligible for the EHLS at School Study over a three-year period between 2016 and 2018. Recruitment is currently underway. At study commencement in 2016, all eligible participants (*n* = 990) were sent an information pack describing the study. The pack contained an information letter, contact details form, brochure describing the EHLS at School Study, EHLS at School fridge magnet, flyer describing the findings from the original EHLS Study, and reply paid envelope. Participants were invited to update their contact details via post, email, or phone. Following the mail out, the study team attempted to contact all participants via phone. If participants had already updated their contact details, the purpose of the phone call was to select an age-appropriate children’s book to be posted to the study child. Otherwise, the phone call was used to introduce the study and update participant details (and subsequently arrange for the book to be posted).

Participants are currently being re-contacted prior to the age of eligibility (7.5 years) to arrange and conduct a home visit assessment. Participants who have moved interstate, overseas or who declined a home visit were offered an online or hardcopy option for completing the questionnaire aspects of the assessment. All participants received a $50 gift voucher on completion of the home assessment, or alternatively, a $30 voucher on completion of the parent questionnaire only. To maintain engagement, study children who have not yet been assessed are sent a birthday card each year. Following the home visit or online assessment, and with written parental consent, school teachers are contacted via email and/or phone and invited to complete an online questionnaire.

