Student Teacher Relationship	The Pianta Student Teacher Relationship Scale [54] assesses teacher’s perception of teacher-child interactions, including warmth, irritability, compliance, and communication (15 items).	Teacher questionnaire (7.5 years)

Multi-method data collection for the EHLS at School study includes a home visit assessment and an online teacher questionnaire at 7.5 years. The home visit involves completion of a parent questionnaire, parent-child observation, and direct child assessment. Also at the 7.5 year home visit, parent permission is obtained for data linkage to retrospective state educational records of school readiness and academic skills at age 5 years, and prospective national academic test results for assessments conducted when children are in Year 3 (age 8) and Year 5 (age 10) of school. Where possible, measures are consistent across the different methods of assessment. For example, the Strengths and Difficulties Questionnaire, a measure of child socio-emotional development, will be accessed via data linkage to provide parent-report data on child outcomes at age 5, and is also collected at age 7.5 years using parent- and teacher-report questionnaires. Study data are collected and managed using REDCap electronic data capture tools hosted at La Trobe University and the Murdoch Childrens Research Institute (Melbourne, Australia). REDCap (Research Electronic Data Capture) is a secure, web-based application designed to support data capture for research studies [32].

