### Progress

As of May 2017, the research team has attempted contact with all eligible participants (*n* = 990), of which 637 (64%) have agreed to further contact when their child reaches the eligible age, and 128 (13%) have declined or ‘passively refused’ (i.e., maximum attempts to contact reached with no participation). Further attempts to make contact will continue for the remaining 225 (23%) participants. Assessments have been completed for 373 participants. Of these, 16 participants did not complete the home assessment but instead provided data in the form of the online parent and teacher questionnaires, and consent for data linkage. So far, more than 90% of parents have consented to completion of the online teacher questionnaires, and to data linkage. Based on completed fieldwork, we anticipate a final sample with complete child and parent data of between 60% and 65% of the initial sample.

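### Follow-up is limited to about half of the toddler-trial families by events after allocation; linkage consent is described only for families who take part at 7.5 years, and the stated adjustment does not address selection into follow-up

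*Protocol article*

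**What the plan says.** Under Eligibility criteria, the 1226 toddler-trial participants are narrowed to those "who completed an assessment prior to, and post intervention, or at the 32 week follow-up". The sentence can be parsed in more than one way, but on any reading an assessment made after allocation is required. The section adds: "Participants who declined to be contacted for future research or those who actively withdrew from the EHLS were excluded".

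Recruitment strategy gives the result: "all eligible participants (*n* = 990) were sent an information pack describing the study". Power calculation cites earlier retention ("78% to 32 week follow-up") and expects 65% of eligible families to take part, stated as 212 standard and 455 *smalltalk*. Progress says: "we anticipate a final sample with complete child and parent data of between 60% and 65% of the initial sample".

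Outcome measures (text after Table 2) states that at the 7.5-year home visit "parent permission is obtained for data linkage to retrospective state educational records of school readiness", and likewise for the later national test results. Progress adds that 16 families without a home assessment supplied online questionnaires and also consented to linkage. Data linkage says that consent is sought separately for each linkage.

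Statistical analyses plans unadjusted and adjusted as-treated comparisons. The adjustment is for characteristics that differ between exposed and unexposed participants; the examples are child age, parent age and mental health, and family demographics.

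**The concern.** Completing a later assessment, withdrawing, refusing further contact and taking part at age 7.5 all come after allocation. Each may depend on which programme a family was offered and on how the family is doing. If it depends on both, comparing those who remain can mislead even if exposure were otherwise comparable. Aim 1 asks for the effect of *smalltalk*, so this bears on the main question.

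There is a second, more practical loss. The school-entry and national test records are collected routinely. A family unwilling to have a visit or fill in a questionnaire could still be followed through them, but only if someone asks for consent. No later analysis plan can recover records for which consent was never sought.

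**Working it through.** **Inputs.** Cohort 1226 (Eligibility criteria); eligible 990 (Recruitment strategy); planned 212 + 455 = 667 at 65% participation (Power calculation); final sample 60% to 65% of the initial sample, and 637 agreed, 128 declined or passively refused, 225 outstanding as of May 2017 (Progress).

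**The plan's own figure.** 0.65 × 990 = 643.5, not 667. 667/990 = 67.4%, and 667/0.65 = 1026. The stated number and the stated percentage do not match, so both are carried forward.

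**Share of the cohort analysed.**
- Eligible: 990/1226 = 80.8%; removed before re-contact: 1226 − 990 = 236 (19.2%).
- At 60% of 990: 594/1226 = 48.5%.
- At 65% of 990: 644/1226 = 52.5%.
- At the stated 667: 667/1226 = 54.4%.
- Cross-check: 637 agreed to further contact, 637/1226 = 52.0%.

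**The denominator in Progress.** If *initial sample* meant 1226, then 60% to 65% would be 736 to 797 families, or 74% to 80% of the 990. On top of all 637 who had agreed, that needs 99 to 160 of the 225 outstanding families. It is not impossible (637 + 225 = 862), but it does not fit the planned 667. Reading it as the 990 does.

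**Where the loss occurs.** With 667 analysed, 1226 − 667 = 559 are lost: 236 through the eligibility rules and 990 − 667 = 323 through non-participation. With 644 or 594 analysed, the second figure is 346 or 396. The readable text does not split the 236 by reason, and gives no losses by arm.

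**Linked outcomes.** The two routes to linkage consent that are described are the home visit (Outcome measures) and the questionnaire-only assessment (the 16 families in Progress). A family that declines both has no described route. On the figures above, the eligible non-participants number 323 to 396. This is an upper limit on what a linkage-only offer could recover. In May 2017 the 128 and the 225 together made 353 of 990 (36%), but the 128 include families never reached after the maximum number of attempts. In addition, the age-5 records cover government schools only (Data linkage).

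**What baseline data can and cannot do.** The behaviour can be shown by simulation, but every selection strength in it is an assumption. Take 1,000,000 families, 54.4% retained in each arm, and an outcome with SD 1 that depends on a measured baseline factor (coefficient 0.5) and an unmeasured one (0.3). Let the log-odds of retention rise by 0.8 per SD of the factor in one arm and 0.2 in the other. Absolute bias in the arm difference, in SD units:

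| Retention depends on | Unadjusted | Baseline-adjusted |
|---|---|---|
| Measured factor, equally in both arms (0.5 each) | about 0.00 | about 0.00 |
| Measured factor, differing by arm | 0.11 | about 0.00 |
| Unmeasured factor, differing by arm | 0.07 | 0.07 |
| Both, differing by arm | 0.16 | 0.06 |

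The pattern is the lesson. Selection that acts alike in both arms does little harm to the difference; measured selection can be removed; unmeasured selection cannot. The sizes are not estimates for this study.

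**The case against.** The strongest reply has four parts.

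*Missing-data methods belong in an analysis plan.* This is right. A condensed article may leave weighting or imputation to a document not shown. A reader might infer that their absence is an error; it is not, and the second change below is a recommendation only.

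*The planned regression already does much of the work.* This is partly right. Adjusting for parent age, mental health and demographics absorbs selection acting through them, as the simulation shows. However, baseline home environment and parent-child interaction are not among the examples given, and the article does not say whether baseline or 7.5-year values will be used. Aim 4 also expects benefit to differ between families, in which case an adjusted average among participants need not be the average for the cohort.

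*The primary contrast is as-treated, so random allocation is already set aside.* This is also right. A reader might infer that attrition alone breaks a randomised comparison, or that baseline data would restore one. The documents support neither. Selection into follow-up is a further source of bias on top of self-selected exposure.

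*Families who withdrew or refused contact cannot be pursued.* This stands and limits the linkage offer. The offer is for eligible families who decline only the 7.5-year assessment.

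Two other inferences are tempting. One is that the most disadvantaged families will be the ones lost. The article gives no attrition data by disadvantage, and every enrolled family met at least one risk criterion. The other is that the eligibility rule causes most of the loss; at 667 analysed, non-participation accounts for more (323 against 236).

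**Conclusion.** The point holds in a limited form. Eligibility rests on conduct after allocation, and about 48% to 54% of the 1226 toddler-trial families will be analysed, taking *initial sample* to mean the 990. The stated adjustment is aimed at exposed-versus-unexposed differences among participants. Selection into follow-up is therefore a real risk, but its size and direction cannot be computed, because the readable text gives no eligibility, participation or outcome data by arm for the families lost.

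The firmest part is the consent route. As described, families who decline both visit and questionnaire also lose linked outcomes that require neither. That is settled in the protocol and is avoidable for those who can still be reached. The conclusion assumes that no linkage-only route exists outside the article. The 1226 are families within randomised clusters, not individually randomised families.

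**What to change.** 1. **Linkage-only consent.** Offer it to those of the 990 who decline both the visit and the questionnaire and can still be reached. Leave out families who withdrew from the original trial or refused further contact. Consent is already separate for each linkage, more than 90% of parents so far have agreed to it, and it has been obtained without a home visit. Cost: a short ethics amendment and a consent form.

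2. **Pre-planned sensitivity analysis for participation.** Weight participants by the inverse of their probability of taking part, or multiply impute, using baseline demographics, parent mental health, home environment and parent-child interaction, for the 1226 families where permission allows. State that this reduces only selection explained by measured factors. Cost: analysis time and possibly slightly wider intervals.

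3. **Wording.** Say which number the *initial sample* in Progress refers to, and reconcile 667 with 65% of 990. Cost: none.
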